#### Support

Women in the intervention group will also have access to their named research midwife or the project manager by telephone throughout the study period; however the research midwives will not initiate contact with participants outside the scheduled intervention or data collection times. Support is to clarify or discuss any considerations for the woman around her forthcoming birth. Women will be advised that contact for support with the research midwife can occur within 9 am to 8 pm. Participant initiated telephone calls will be diarised to include the woman’s gestation, issues raised, the content of responses provided, and duration of calls. The importance of an accessible source of information for women to talk about their upcoming birth has recently been demonstrated in the uptake of a telephone service within a tertiary setting [41].

Although the majority of women prefer a vaginal birth, recruitment and intervention close to the woman’s first antenatal hospital appointment may encourage women to consider their options earlier. However a strategy to support women to negotiate the maternity system across the pregnancy is required. In one study women planned a vaginal birth at 36 weeks gestation but Shorten et al. [29] identified that organisational culture impacted women securing their preferred mode of birth. Consistent support may minimise the likelihood of women consenting to a birth option that differs from their preference, and this might be particularly important given it has been reported that anxiety in women is higher around 37 weeks [42]. Therefore, along with access to ongoing telephone support, a second counselling intervention will occur after 34 weeks and prior to the routine36 week antenatal appointment with a medical practitioner. This session will consolidate strategies women may like to adopt in order to clarify, or secure, their preferred mode of birth at time of next appointment. While the purpose of the study is to reduce fear, support women’s decision making and subsequently improve vaginal birth rates, the intervention is most importantly to assist women to develop strategies for a positive birth experience regardless of the ultimate mode of birth.

### Midwife training for the psycho-education counselling intervention

The training program includes two intensive 4 hour workshops, written manuals, web-based resources, a DVD of counselling skill vignettes related to the counselling framework, personal supervision of undertaking the counselling, and assessment criteria for competence. The quality and effectiveness of the counselling training will be evaluated through supervision processes, integrity checks, regular group meetings with midwives, a client satisfaction survey as well as research measures of clinical effectiveness [34,35]. Maintenance of the midwife researcher’s counselling competency will be monitored throughout the study.

### Integrity/adherence to counselling intervention protocol

Each of the first five telephone interviews for every midwife counsellor will be independently reviewed and rated for adherence to the counselling strategy.

### Quality and safety

For consistency of the intervention and to determine ongoing competency of the midwives' counselling skills all participants in the intervention group will be asked for permission and their written consent to audio tape the intervention. Members of the research team as well as the project manager (herself skilled in the intervention) will review the counselling intervention for quality and adherence to the intervention.

Participant recruitment and retention will be reviewed monthly and monitored against study timeframes, the intention of the research, for feedback from participants, and to monitor outcome indicators along with any adverse events. A risk assessment will be observed with any distressed women referred via the hospital’s usual processes for appropriate psychosocial intervention in consultation with the obstetric and perinatal mental health team, with the woman withdrawn from the study.

### Data collection

Data collection is shown in the flow diagram (Figure 1). Data will be collected at 3 time points; Recruitment ≈ 20 weeks (T1), 36 weeks gestation, (T2), 4–6 weeks postpartum (T3). Women will be given the option of completing via the post or via telephone. In our previous studies, telephone interviews facilitated a good response rate and were a reliable and accurate way of collecting information. They were also considered preferable by participants given the demands and unpredictability of new motherhood.

**Figure 1 F1:**
[figure not shown]
Key points for data collection.

### Data management and analysis

The commercial product Remark Office OMR [43] will be used to export raw data from the study tools into the Statistical Package for the Social Sciences (SPSS), minimizing data entry errors. Relationships between categorical variables will be examined using chi-square analyses, between continuous variables Pearson’s product moment correlation test and for relationship between continuous and categorical variables one-way ANOVA of variance. An alpha level of 0.05 will be used for all statistical tests with bonferonni correction where applicable.

A preliminary analysis will examine the pattern of responses to demographic items, and to scales and subscales. The purpose of this analysis is to identify factors that might be influential in determining subscale and scale scores regardless of treatment group. Where necessary, equivalent non-parametric procedures will be used. The issue of missing data owing to participant dropout will be addressed using either multiple imputation or a direct maximum likelihood approach to estimation. These procedures represent the current state of the art in handling missing data in RCTs [44]. In this way, power is maximised by using all available data points in a statistically appropriate manner. Potentially confounding variables such as age, and parity can be entered into the statistical models to adjust for any impact.

Analysis of covariance (ANCOVA) will compare post-treatment scores for the intervention and control groups, with the baseline score as the covariate. Secondary analyses will include a series of independent group t-tests to compare change scores (baseline minus treatment) for the intervention and control groups for other outcomes measures. The chi square statistic will compare percentages of cases in the intervention and control groups who improved, remained the same, or deteriorated.

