## Background

The prevalence of fear associated with childbirth is around 20% with approximately 6-10% of women experiencing intense fear of labour and birth that is dysfunctional or disabling [1]. A further 13% of non-pregnant women are fearful enough of childbirth to postpone or avoid pregnancy [2]. Childbirth fear has received considerable attention in Scandinavian countries, and the UK [3-6] but not in Australia. Our previous qualitative and quantitative work suggests that levels of childbirth fear are significant. For example, in our large qualitative study (n = 202) approximately 22% of mothers used words such as *terrifying* and *petrifying* to describe their expectations of birth [7,8]. Our subsequent survey of 400 pregnant women using the Expectations and Experiences Questionnaire (WDEQ) [9] found that nearly 50% of women reported moderate fear and 26% reported intense fear of childbirth [10]. These figures are much higher than those reported in Scandinavian studies.

While most studies have found nulliparous women to be more fearful than multiparous women, the reverse has also been demonstrated [11-13]. While this fear is commonly associated with concern for the baby it is also related to uncertainly about the unknown [14]. For some first-time pregnant women a perceived lack of control mixed with a disbelief in the body’s ability to give birth safely becomes overwhelming and generates extreme fear; referred to as primary childbirth fear [11,15]. When multiparous women admit fear it is often a result of a previous negative and/or traumatic birth experience [13]. This is described as secondary fear or tocophobia [16].

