### Outcome measures

The primary outcome measure is a reduction in childbirth fear according to the Wijma Delivery Expectancy/Experience Questionnaire. Secondary outcome measures include the Decisional Conflict Scale, Edinburgh Postnatal Depression Scale, Childbirth Self-Efficacy Inventory, EuroQol 5 dimensional scale, mode of birth, and health service use.

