### Setting

Gold Coast, Logan and Redland Hospitals are large facilities in South-East Queensland, Australia with approximately 8,500 births per year.

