### Sample and sample size

Pregnant women in their 2nd trimester (12–24 wks) will be invited to participate. Using a significance level of 5%, power of 80%, and a two-tailed test, a sample of 150 participants in each group is required (recruitment approx n = 1200 women prior to randomisation). The sample size calculation assumes that around 20% of women at recruitment (approximately 20 weeks gestation) will report high levels of fear [10] and consent to participate. Calculations for recruitment allowing for loss to follow-up are based on a formula derived from our previous work. Expected number of eligible women per month = 466. Some women may be missed or lost to follow-up and we expect an attrition rate of 30%.

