### Recruitment protocol & randomisation procedure

The research midwives will follow a recruitment protocol which adheres to the National Health and Medical Research Council ethical guidelines for human research. Clinic staff will be briefed on the project and invite eligible women to speak to the research midwife attending the antenatal clinic. After obtaining informed consent, women will be invited to provide contact details and complete a questionnaire. Questionnaire responses will be scored. Within 72 hours, women who score ≥66 on the WDEQ-A will be contacted and with their permission randomised into the intervention or control group using a centralised block randomisation with stratification for different sites and parity with a 1:1 allocation. The research-midwife will access the web-based randomisation service after gaining participant’s written consent and not blinded to the woman’s allocation.

Women receiving the BELIEF intervention will be offered a convenient time for the first of two telephone counselling sessions. Participants will also be provided with a contact telephone number (available 9 am-8 pm) if they require additional support. Details of this contact will be logged.

All women will be monitored for psychological safety by research staff. We have developed a risk protocol that clearly sets out referral pathways. Participation is not expected to disadvantage any women. Women receiving the intervention are expected to have reduced psychological distress and women in the control group will be monitored and receive scheduled measurement of their psychological well-being. Women will be referred to pre-arranged counselling services if necessary and excluded from the study but included in the intention-to-treat analysis. Although the research midwife will not be blinded to group allocation, follow-up assessment will be conducted by an independent research assistant not involved in the intervention. Additionally analysis will be blinded.

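### Randomisation is stratified by site and parity, but the stated ANCOVA adjusts only for baseline, never names site and leaves parity optional

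*Protocol article*

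**What the plan says.** All places are in the protocol article.

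- **Recruitment protocol & randomisation procedure:** allocation is by "centralised block randomisation with stratification for different sites and parity with a 1:1 allocation". The Setting section names three hospitals.
- **Outcome measures:** "The primary outcome measure is a reduction in childbirth fear according to the Wijma Delivery Expectancy/Experience Questionnaire".
- **Data management and analysis, main model:** "Analysis of covariance (ANCOVA) will compare post-treatment scores for the intervention and control groups, with the baseline score as the covariate". The next sentence gives secondary analyses (t-tests on change scores) to the other outcomes, so the ANCOVA is evidently the primary-outcome model.
- **Data management and analysis, other covariates:** "Potentially confounding variables such as age, and parity can be entered into the statistical models to adjust for any impact". The list is open, no rule says when a covariate enters, and site is not mentioned.
- **Data management and analysis, preliminary step:** an initial look at response patterns is planned. "The purpose of this analysis is to identify factors that might be influential in determining subscale and scale scores regardless of treatment group".
- **Background:** parity is linked to the level of fear ("While most studies have found nulliparous women to be more fearful than multiparous women"), with the remark that the opposite has also been found.

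**The concern.** Parity is treated as a design factor when women are allocated, and as a possible confounder that may or may not be adjusted for when they are analysed. Site is a design factor at allocation and absent from the analysis. Two things follow.

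First, stratified allocation removes between-stratum variation from the true sampling error of the arm difference. A model without the strata leaves that variation in its residual, so it reports a standard error larger than the true one. Confidence intervals are then too wide and some power is lost.

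Second, if age and parity are optional, the primary comparison could be reported with neither, either one or both. That is four versions of one result, with no stated rule for which of them counts.

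**Working it through.** **Inputs from the article.** Strata are site (three hospitals) and parity. Allocation is 1:1. The test is two-sided at 5% with 80% power and 150 per group. Expected attrition is 30%.

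**Assumptions, because the article gives no figure.** There are two parity classes, so 3 × 2 = 6 strata, and the block size is 4. R² is the share of the variance left after baseline adjustment that the strata explain, taken as 0 to 0.20 with 0.05-0.10 as the working range.

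**1. The article's own figure.** The 150 per group cannot be reproduced, since no effect size or standard deviation is stated. Solved backwards, the standardised difference it can detect is d = (1.960 + 0.842) × √(2/150) = 0.3235. This d is used below only as a reference effect, in units of the standard deviation left after baseline adjustment.

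**2. Reported against true standard error, strata omitted.** In large samples the ratio is 1/√(1 − R²). The actual type I error is 2 × [1 − Φ(1.96/√(1 − R²))].

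| R² | Reported SE too large by | Actual type I error |
|---|---|---|
| 0 | 0% | 5.0% |
| 0.02 | 1.0% | 4.8% |
| 0.05 | 2.6% | 4.4% |
| 0.10 | 5.4% | 3.9% |
| 0.20 | 11.8% | 2.8% |

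**3. Power at 150 per group, d = 0.3235.** The expected z-value on the unadjusted scale is 2.802.

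- Strata omitted: Φ[(2.802 − 1.96)/√(1 − R²)].
- Strata included: Φ[2.802/√(1 − R²) − 1.96].
- R² = 0.05: 80.6% against 82.0%, a loss of 1.4 points.
- R² = 0.10: 81.2% against 84.0%, a loss of 2.7 points.

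**4. Simulation check.** Block randomisation in six strata, 300 women in total, 4,000 runs under the null and 2,000 for power.

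| R² | Type I error, strata omitted → included | Power, strata omitted → included |
|---|---|---|
| 0.05 | 0.050 → 0.056 | 0.813 → 0.828 |
| 0.10 | 0.043 → 0.055 | 0.809 → 0.841 |
| 0.20 | 0.033 → 0.051 | 0.815 → 0.875 |

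The power differences of 1.5 and 3.2 points at R² of 0.05 and 0.10 agree with step 3. The simulated type I errors carry a Monte Carlo error of about √(0.05 × 0.95/4000) = 0.003, so the small departures from 5% in the model with strata, and from 4.4% at R² = 0.05 without them, are not to be read closely.

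At R² = 0.10 without strata, the mean reported standard error is 0.1156 and the empirical one 0.1112. With strata they are 0.1096 and 0.1110. The estimate therefore varies by the same amount either way (0.1112 and 0.1110), and only the reported standard error is wrong.

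With 210 women (300 less 30%), the power differences are 2.0 points (0.640 to 0.660) at R² = 0.05 and 4.1 points (0.658 to 0.699) at R² = 0.10.

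**5. The optional covariates.** A second simulation (6,000 runs per setting) fitted four models: baseline only, plus parity, plus age, plus both. Age and parity each explained 2-10% of the post-baseline variance. Always reporting the smallest of the four p-values gave a type I error of 0.053 to 0.066, against 0.039 to 0.047 for the baseline-only model held fixed. This is a worst case, not a forecast.

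**The case against.** The strongest reply is that a condensed article need not list every covariate. That stands for missing detail, but the article is not silent: it states a model without the design factors and says that parity may be entered. A later analysis plan that fixed both factors would have to override this wording.

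Three stronger readings are tempting, and the documents do not support them.

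- **Covariates will be chosen after an exploratory search.** A reader might join the preliminary analysis to the covariate sentence in the same paragraph. The text never does. The preliminary step has its own purpose and is pooled over arms, sentences on non-parametric methods and missing data come between, and age and parity are named without reference to its results. The randomisation section also promises blinded analysis, which limits choosing a model to favour an arm. It cannot be said that the confirmatory p-value is undermined.
- **The precision bought by stratification is thrown away.** Step 4 shows that it is not. The estimate keeps its precision and only its reported standard error is too wide.
- **No primary model is stated.** The ANCOVA on baseline is worded as a commitment, and the covariate sentence can be read as supplementary adjustment. What remains open is whether an adjusted version could take its place.

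The assumed 5-10% can also be questioned. The Background links parity to the level of fear with mixed direction, entry is restricted to women scoring 66 or more, and adjustment for baseline may absorb much of any parity effect. Nothing in the article suggests that site is prognostic. This limits the size of the point, not its direction.

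**Conclusion.** The point holds as a modest one. The stated analysis departs from the stated randomisation: site is absent from it and parity is left to discretion.

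For an assumed R² of 0.05-0.10, the reported standard error is 2.6-5.4% too large, the actual type I error is about 4.4-3.9%, and about 1.5-3 points of power are lost at 150 per group. The error is conservative, so it does not threaten the validity of a positive result, and it disappears if the strata predict nothing beyond baseline. The power figures rest on a d worked back from the sample size.

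The discretionary wording is a separate and smaller weakness. It leaves room for several adjusted results, and even deliberate selection among four models raised the type I error to at most about 0.066 in the settings tried. The correction is worth making because it is cheap and brings the analysis into line with the design.

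**What to change.** State one primary model: follow-up W-DEQ-A on arm, baseline W-DEQ-A, site (three levels) and parity, fixed before unblinding. Either name age in advance as a covariate or move it, with any other covariate, to a labelled sensitivity analysis. Add that the preliminary analysis is descriptive and plays no part in choosing the model.

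For continuous secondary outcomes, use the same ANCOVA form with each outcome's own baseline where one exists. This replaces the stated t-tests on change scores, so it is a change of method and should be written as one. The same covariates should not be imposed on every outcome without thought: for a binary outcome such as mode of birth, covariate adjustment by logistic regression changes the odds ratio being estimated.

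For the primary model the cost is a sentence or two of text and about three degrees of freedom (two for site, one for parity). Both factors must already be known at randomisation, so no new data are needed.

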### Postnatal questionnaire – 4–6 weeks postpartum

Data will be collected on maternal and neonatal outcomes including mode of birth, use of interventions such as induction, anaesthesia (e.g. epidural) and neonatal outcomes. Participants will be asked about their experience of labour, birth, and postnatal care, involvement in decision making, satisfaction with care, and future birth plans. This questionnaire will be adapted from the QCMB Survey – Having a Baby in Queensland [31]. This information will enable comparison with the birthing population in Queensland.

*Parenting Sense of Confidence and Satisfaction (PSOC - 12 items)* measures self-efficacy and satisfaction derived from parenting and is commonly used [32]. Only the self-efficacy factor (7 items, 6-point Likert scale) will be used. This factor has good internal consistency (α .76) (62) with higher scores indicating stronger self-efficacy.

*Health service use (HSU)* The use of health services (GP visits, emergency department attendances and hospital admissions) by both the mother and the baby will be collected retrospectively. Health service use by the mother and baby will be obtained from Medicare Australia for the period from 20 weeks gestation to 4 to 6 weeks follow-up. The diagnosis and Australian Refined Diagnostic Related Group (AR-DRG) will be collected for all reported admissions to hospital for the same period. We have used these scales previously with the Australian childbearing population. The questionnaires take approximately 40 minutes to complete.

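### Secondary scales are compared by unadjusted change-score t-tests, which give away precision that the plan's own baseline-adjusted ANCOVA would keep at no cost.

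*Protocol article*

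**What the plan says.** Under Data management and analysis, the protocol article first sets out the adjusted comparison: "Analysis of covariance (ANCOVA) will compare post-treatment scores for the intervention and control groups, with the baseline score as the covariate". The next sentence changes method for the remaining outcomes: "Secondary analyses will include a series of independent group t-tests to compare change scores (baseline minus treatment"). A third sentence adds a categorical comparison: "The chi square statistic will compare percentages of cases in the intervention and control groups who improved, remained the same, or deteriorated". The same section sets the error rate: "An alpha level of 0.05 will be used for all statistical tests with bonferonni correction where applicable".

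Under Outcome measures, W-DEQ fear is primary. The secondary outcomes are the Decisional Conflict Scale, EPDS, Childbirth Self-Efficacy Inventory, EQ-5D, mode of birth and health service use. Parenting self-efficacy is not in that list. It is described only in the postnatal questionnaire section, where the article says "Only the self-efficacy factor (7 items, 6-point Likert scale) will be used".

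Under Sample and sample size: "Using a significance level of 5%, power of 80%, and a two-tailed test, a sample of 150 participants in each group is required", and "we expect an attrition rate of 30" per cent. No effect size, SD or baseline/follow-up correlation is given. Randomisation uses "stratification for different sites and parity with a 1:1 allocation".

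**The concern.** Two adjacent sentences use the baseline in different ways. ANCOVA estimates how strongly follow-up depends on baseline and removes that part. A change score fixes the slope at 1 whatever the data show. Unless the true slope is 1, this leaves noise that ANCOVA would remove.

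The hypotheses on decisional conflict, depressive symptoms and childbirth self-efficacy rest on these secondary scales. If the correlation over the roughly 16 weeks from recruitment to 36 weeks' gestation is moderate, those hypotheses are tested with avoidably low power, and a null result would be harder to interpret.

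The change-score sentence also names the other outcome measures without exception. Some of these (mode of birth, health service use) have no pre-treatment value from which a change could be formed, so the scope of the sentence needs stating.

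**Working it through.** **Inputs from the article.** Two-sided alpha 0.05, 80% power, 150 per group, 1:1 allocation, 30% attrition.

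**Assumed.** Baseline/follow-up correlation r = 0.3, 0.5 and 0.7; equal SDs at both times, set to 1; normal approximation; no Bonferroni correction.

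**Step 1: the plan's own figure.** 150 per group cannot be reproduced, because no effect size or SD is stated. It can only be inverted for an unadjusted two-group comparison:

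d = (1.960 + 0.842) × √(2/150) = 2.802 × 0.1155 = 0.3235 SD.

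This serves below as a reference effect. The article does not claim it for any secondary scale.

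**Step 2: variance per woman.**

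- Change score: 2(1 − r)
- ANCOVA: 1 − r² = (1 − r)(1 + r)
- Ratio, change score to ANCOVA: 2/(1 + r), which exceeds 1 for every r below 1

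| r | change score | ANCOVA | ratio |
|---|---|---|---|
| 0.3 | 1.40 | 0.91 | 1.54 |
| 0.5 | 1.00 | 0.75 | 1.33 |
| 0.7 | 0.60 | 0.51 | 1.18 |

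The same ratio applies to sample size. To match ANCOVA on 150 per group, the change-score test needs 231, 200 and 177 per group.

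**Step 3: power at d = 0.3235.** Power = Φ(d/SE − 1.960), with SE = √(2 × variance / n). The smaller n is 150 × 0.70 = 105, which applies if the 30% comes off 150.

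Worked case, r = 0.3 and n = 105:

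- Change score: SE = √(2 × 1.40/105) = 0.1633; d/SE = 1.981; power = Φ(0.021) = 51%
- ANCOVA: SE = √(2 × 0.91/105) = 0.1317; d/SE = 2.457; power = Φ(0.497) = 69%

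| n per arm | r | change-score t-test | ANCOVA |
|---|---|---|---|
| 105 | 0.3 | 51% | 69% |
| 105 | 0.5 | 65% | 77% |
| 105 | 0.7 | 86% | 91% |
| 150 | 0.3 | 66% | 84% |
| 150 | 0.5 | 80% | 90% |
| 150 | 0.7 | 95% | 97.5% |

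**Step 4: comparison with ignoring baseline.** The follow-up score alone has variance 1. When r is below 0.5, 2(1 − r) exceeds 1, so subtracting the baseline is worse than not using it: at r = 0.3 and 105 per arm, 51% against 65%.

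**The case against.** The strongest reply is that these are secondary outcomes and the chosen test is valid. That stands: under randomisation the change-score t-test is unbiased, so only precision is at issue. The size of the loss rests on a correlation that the article does not give, and at r = 0.7 with 105 per arm it is only 5 power points. The figure of 105 is also uncertain. The article says its recruitment calculations allow for loss to follow-up, and it plans multiple imputation or likelihood methods that use all available data. Both sample sizes are therefore shown. The article also lets age and parity enter the models, so adjustment is contemplated, but an independent-groups t-test has no place for a covariate. The direction of the loss does not depend on any of this.

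Three stronger readings are tempting and are not supported:

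- **That outcomes without a baseline have no usable analysis.** The same section assigns chi-square to categorical variables, one-way ANOVA to continuous-by-categorical relationships, and non-parametric equivalents where needed. These can serve mode of birth, health service use and parenting self-efficacy. What remains is that the change-score sentence should say it does not cover them.
- **That the three-category chi-square cuts at zero change and mainly shows regression to the mean after selection at W-DEQ-A ≥66.** The article states no cut-off and ties the test to no outcome. Category definitions are detail that an article may leave to the full protocol. Regression to the mean would also act in both randomised arms.
- **That ANCOVA is expressly confined to the primary outcome.** The ANCOVA sentence names no outcome. That it applies to W-DEQ is inferred from the words that follow about other outcome measures.

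**Conclusion.** The point holds as a loss of precision on the continuous secondary scales that have a recruitment value, meaning those among decisional conflict, EPDS, childbirth self-efficacy and EQ-5D measured then. The data-collection figure is not shown, so which scales qualify cannot be confirmed here.

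For correlations of 0.3 to 0.7, the change-score variance is 54% to 18% larger than that of ANCOVA. At the reference effect this costs about 18 down to 5 power points with 105 per arm, and about 18 down to 2 with 150. These sizes assume equal variances, the stated correlations, an effect of 0.32 SD and an uncorrected 5% level. That ANCOVA is the more precise follows from the algebra for any r below 1 with equal variances. The finding does not concern bias and does not touch the primary comparison. It is a free improvement.

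**What to change.** 1. Replace the change-score t-tests by the ANCOVA already planned. For every continuous secondary outcome with a baseline, regress the post-treatment score on arm, baseline score, and the stratification factors site and parity.
2. State that outcomes with no pre-treatment value (mode of birth, health service use, parenting self-efficacy) are compared directly between arms, adjusted for site and parity, and fall outside any change-score sentence.
3. Keep the improved/same/deteriorated chi-square as descriptive only.

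The cost is a few sentences in the analysis section. No further data, visits or participants are needed.

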### Hypotheses

1) Relative to controls, women receiving BELIEF will report lower levels of childbirth fear at term; 2) less decisional conflict; 3) less depressive symptoms; 4) better childbirth self-efficacy; and 5) improved health and obstetric outcomes.

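### Minor: the improved / same / deteriorated comparison uses a chi-square that ignores category order; an ordered test with a directional estimate would serve better at almost no cost

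*Protocol article*

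**What the plan says.** In the protocol article, under Data management and analysis, the main comparison is an ANCOVA of post-treatment scores with the baseline score as covariate. T-tests on change scores follow for the other outcomes. The last sentence adds a three-category comparison: "The chi square statistic will compare percentages of cases in the intervention and control groups who improved, remained the same, or deteriorated". The same section makes the chi-square the general tool for categorical data: "Relationships between categorical variables will be examined using chi-square analyses".

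No trend, rank or ordinal method is named for the three categories. The one flexible phrase, "Where necessary, equivalent non-parametric procedures will be used", stands in the paragraph on preliminary analysis and is not tied to this comparison. The error level is given as "An alpha level of 0.05 will be used for all statistical tests with bonferonni correction where applicable".

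The first hypothesis has a direction: "women receiving BELIEF will report lower levels of childbirth fear at term". The sample size section states "Using a significance level of 5%, power of 80%, and a two-tailed test, a sample of 150 participants in each group is required" and adds "we expect an attrition rate of 30" per cent. Randomisation is described as "centralised block randomisation with stratification for different sites and parity with a 1:1 allocation".

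**The concern.** Improved, same and deteriorated form an ordered scale, and the trial asks whether BELIEF moves women towards the better end. A 2-df chi-square gives the same p-value however the three labels are permuted. It spreads its sensitivity over every kind of difference between the arms and yields no estimate that says which arm did better.

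Two things are at stake. First, some power is lost if the benefit is a general shift. Second, a p-value from this table cannot by itself separate benefit, harm and polarisation. This is the only comparison in the article that puts deterioration side by side between arms, and its percentages are easy for clinicians to read, so it is worth making the result interpretable.

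**Working it through.** **Inputs from the protocol article.** Two-tailed 5% level, 80% power, 150 per group, 1:1 allocation and 30% attrition. If 150 is the number randomised, 150 × 0.70 = 105 per arm remain. The text does not settle this, so both sizes are used.

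**Inputs assumed.** The article gives no category percentages, effect size or SD. Control splits and effects below are therefore assumptions, shown over a range. All splits are improved / same / deteriorated.

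**The plan's own figure.** Without an effect size, 150 per group can only be inverted: d = (1.960 + 0.842) × √(2/n). This gives d = 0.32 for n = 150 and d = 0.39 for n = 105. The article states neither value. They do make 0.3 to 0.4 SD a sensible range to examine.

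**Step 1: the statistic carries no direction (150 per arm).**
- 60/60/30 with BELIEF against 45/60/45: chi-square 5.14 on 2 df, p = 0.076. The Wilcoxon test gives p = 0.025.
- The mirror image in harm, 30/60/60 against 45/60/45: again chi-square 5.14, p = 0.076.
- 60/30/60 against 45/60/45, where improved minus deteriorated is zero in both arms: chi-square 14.29, p = 0.0008. Wilcoxon p = 1.00.

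**Step 2: power when both boundaries move.** Take a control split of 50/25/25 and a common odds ratio of 1.8.
- Odds of improved: 1.0 × 1.8 = 1.8, so 64.3%.
- Odds of improved or same: 3.0 × 1.8 = 5.4, so 84.4%.
- BELIEF split: 64.3/20.1/15.6.

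The chi-square noncentrality is n Σ(a − b)²/(a + b), where a and b are the two arms' proportions. At n = 150 this is 150 × (0.01786 + 0.00535 + 0.02164) = 6.73. On 2 df this gives 64% power.

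A linear trend test with scores 1, 0, −1 has mean difference 0.2366 and variance 0.6389 × 2/150 = 0.00852. Its noncentrality is 0.2366²/0.00852 = 6.57, and on 1 df this gives 73%. Nearly all the signal lies in the ordered direction, so the second degree of freedom costs power. Simulating 20,000 tables with the tie-corrected Wilcoxon test gives 74%.

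| Control split | Odds ratio | n per arm | Chi-square | Ordered test |
|---|---|---|---|---|
| 50/25/25 | 1.8 | 150 | 64% | 74% |
| 50/25/25 | 1.8 | 105 | 48% | 58% |
| 30/40/30 | 1.5 | 150 | 38% | 47% |
| 30/40/30 | 1.5 | 105 | 27% | 35% |
| 30/40/30 | 2.0 | 150 | 83% | 89% |
| 30/40/30 | 2.0 | 105 | 67% | 76% |

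Over the splits tried, with odds ratios 1.5 to 2.0 and both sizes, the gain is about 6 to 11 points. A normal shift of 0.3 to 0.4 SD, cut at fixed thresholds, gives about 7 to 11 points. For a purely linear shift where the ordered test has 80% power, the chi-square has 71% and needs about 23% more women (required noncentrality 9.63 against 7.85).

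**Step 3: where the ordered test loses (150 per arm).**

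| Change from control to BELIEF | Chi-square | Rank test |
|---|---|---|
| 50/25/25 to 62/13/25 (only same to improved) | 70% | 33% |
| 50/25/25 to 50/15/35 (only same to deteriorated) | 61% | 13% |
| 30/40/30 to 40/30/30 (only same to improved) | 44% | 20% |
| 30/40/30 to 40/20/40 (both extremes rise) | 93–94% | about 5% |

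**Step 4: what separate differences add.** Take BELIEF 85/20/45 against control 75/45/30. The chi-square is 13.24, p = 0.001, and the rank test gives p = 0.96. With 95% CI = difference ± 1.96 × √[p₁(1 − p₁)/150 + p₂(1 − p₂)/150]:
- Improved: 56.7% − 50.0% = 6.7 points (−4.6 to 17.9).
- Deteriorated: 30.0% − 20.0% = 10.0 points (0.3 to 19.7).

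The two differences show the polarisation, with its direction, where the ordered test alone would miss it.

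**The case against.** The strongest reply is that the chi-square is a recognised and valid test for a 2 × 3 table and that the choice involves a real trade-off. Step 3 bears this out: when only one boundary moves, the ordered test can lose 24 to 48 points, far more than it gains under a general shift. The article gives no category rates that would favour one pattern over another.

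This stands as a limit on the claim. It does not remove the advice, because the categories appear to be cut from change in continuous scores, and a general shift in such scores moves both boundaries. Where it does not, the separate differences proposed below fill the gap.

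A reader might also infer that the plan could declare a false success, since a polarised table is significant under the chi-square. The documents do not support that. In such a table the arms really differ, so rejection is correct, and a rise in deterioration is something a trial that monitors psychological safety would want to see. The percentages per arm, which the plan compares, already show the direction.

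Three further points stand. The article says only chi square statistic, so the unordered 2-df form is the ordinary reading but not an explicit statement. The comparison is supportive: no hypothesis, outcome definition or sample size rests on it. The exact form of a secondary test may also be refined in an analysis plan that is not shown. On the other side, the general non-parametric sentence does not rescue the choice, because it names no ordered test and the chi-square is already non-parametric.

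**Conclusion.** The point holds as an inexpensive improvement of minor severity. The named test, on its ordinary reading, does not use the order of the categories and gives no directional estimate. For a general shift it gives up about 6 to 11 points of power against an ordered test. This rests on assumed control splits, odds ratios of 1.5 to 2.0 or normal shifts of 0.3 to 0.4 SD, and 105 to 150 women per arm.

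It would go too far to call the chi-square wrong or to say that it loses power for every real effect. Type I error stays at 5% when the arms have identical distributions, the loss is confined to shifts that move both boundaries, and the ANCOVA that carries the primary conclusion keeps direction and is untouched.

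**What to change.** Replace the last sentence of Data management and analysis with wording such as: The three ordered categories will be compared between groups with a proportional-odds model, or with a row-mean-score (Wilcoxon-type) test stratified by site and parity, and a common odds ratio with 95% CI will be reported. The percentages in each category will be given per arm, with the between-arm differences in percent improved and percent deteriorated and their 95% CIs.

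The strata are those already used for randomisation. The cost is a sentence or two of analysis wording and no new data. The downside is the weaker performance of the ordered test in the one-boundary and polarised cases shown above. The two separate differences are there to cover it, so they should not be dropped.
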